## Abstract

**Background:**

Lasting disability and further falls are common and costly problems in older people following fall-related lower limb and pelvic fractures. Exercise interventions can improve mobility after fracture and reduce falls in older people, however the optimal approach to rehabilitation after fall-related lower limb and pelvic fracture is unclear. This randomised controlled trial aims to evaluate the effects of an exercise and fall prevention self-management intervention on mobility-related disability and falls in older people following fall-related lower limb or pelvic fracture. Cost-effectiveness of the intervention will also be investigated.

**Methods/Design:**

A randomised controlled trial with concealed allocation, assessor blinding for physical performance tests and intention-to-treat analysis will be conducted. Three hundred and fifty people aged 60 years and over with a fall-related lower limb or pelvic fracture, who are living at home or in a low care residential aged care facility and have completed active rehabilitation, will be recruited. Participants will be randomised to receive a 12-month intervention or usual care. The intervention group will receive ten home visits from a physiotherapist to prescribe an individualised exercise program with motivational interviewing, plus fall prevention education through individualised advice from the physiotherapist or attendance at the group based “Stepping On” program (seven two-hour group sessions). Participants will be followed for a 12-month period. Primary outcome measures will be mobility-related disability and falls. Secondary outcomes will include measures of balance and mobility, falls risk, physical activity, walking aid use, frailty, pain, nutrition, falls efficacy, mood, positive and negative affect, quality of life, assistance required, hospital readmission, and health-system and community-service contact.

**Discussion:**

This study will determine the effect and cost-effectiveness of this exercise self management intervention on mobility-related disability and falls in older people who have recently sustained a fall-related lower limb or pelvic fracture. The results will have implications for the design and implementation of interventions for older people with fall related lower limb fractures. The findings of this study will be disseminated in peer-reviewed journals and through professional and scientific conferences.

**Trial Registration:**

Australian New Zealand Clinical Trials Registry: ACTRN12610000805077.

**Electronic supplementary material:**

The online version of this article (doi:10.1186/s12877-016-0206-5) contains supplementary material, which is available to authorized users.

## Background

Fall-related lower limb and pelvic fractures are common problems with major implications for individuals, their carers, health services and the community. The greatest burden is from hip fractures, and although surgery is generally successful, many people do not fully recover. Most hip fracture survivors do not regain their former levels of activity or mobility and so are at increased risk of further falls. Many also have increased dependence, with approximately 10 % unable to return to their previous residence [1–3]. As the proportion of older rises globally, the costs associated with lower limb and pelvic fractures will increase [4]. Optimising recovery after lower limb fractures and preventing further falls have the potential to reduce the burden on individuals and society. There is systematic review evidence that outcomes after fall-related fractures can be improved with well-designed intervention programs [1, 5–7] but the best approach to improve function is not evident [8]. Current clinical guidelines do not include clear conclusions about the optimal content of rehabilitation programs [9] and systematic reviews provide no consensus on the best type or intensity of exercise after lower limb and pelvic fractures [1, 5, 6].

Existing trials of post-fracture rehabilitation leave many questions unanswered. The interventions that have had the largest effect on mobility and function to date were delivered with high intensity (three times per week) and close supervision in centre-based settings [10, 11]. Such programs are resource intensive and further investigation is indicated to assess whether such gains are possible with less costly interventions. Encouragingly, a recent high-quality randomised trial found a six-month home exercise program, taught by a physiotherapist and undertaken with minimal supervision, improved mobility in older people after hip fracture [12]. This is consistent with previous trials in which home exercise programs taught by physiotherapists improved shorter-term mobility outcomes after hip fracture [13, 14]. Effects on the participation aspect of functioning [15] have not been well investigated to date. Few trials have had intervention periods exceeding six months [16–18] or prolonged follow-up [12]. Considering the evidence for the benefits of ongoing exercise in the older population [19] and de-training once exercise ceases [20], longer intervention and follow-up may be important. Motivational interviewing and self-management approaches have been used in other settings to encourage ongoing intervention adherence but are yet to be well investigated in post hip-fracture populations [21].

Falls remain an important problem in post fracture populations but few trials have evaluated the effect of exercise programs on the prevention of further falls in fracture survivors and the results are conflicting [16, 17, 22]. Bischoff-Ferrari and colleagues found that prescription of home-based exercise by physiotherapists prior to hospital discharge was feasible and that it reduced falls in the following 12 months [17]. Orwig *et al* did not detect a between-group difference in fallers when a home exercise program was compared to usual care [16]. Sherrington *et al* concluded that a home exercise program that did not specifically include fall prevention advice improved mobility (measured with the Short Physical Performance Battery) but actually increased the rate of falls in older people who had recently returned home after hospital stays [22]. There is clearly an urgent need to understand the impact of adding a fall prevention aspect to home exercise programs.

There is potential for a combined home-based exercise and fall-prevention program to be effective and cost-effective in improving mobility and reducing falls following lower limb and pelvic fractures. We have designed such an intervention. The design of this program has been informed by previous research concerning exercise and consumer education for falls prevention and about the role of motivational interviewing and self-management approaches to enhance intervention adherence. Specifically, research suggests that the most effective type of exercise for falls prevention in older people includes a high challenge to balance and a high dose [23], and that the “Stepping On” self-management training program can prevent falls and improve self-efficacy in community-dwelling older people [24].

We will conduct a trial that aims to determine the effect of this exercise and fall prevention self-management training program on mobility-related disability and falls in people with a recent fall-related lower limb or pelvic fracture: the Recovery Exercises and Stepping On after fracture trial (RESTORE) trial. To our knowledge, this is the first study to examine the effect of an exercise and fall prevention self-management program on mobility and falls in older people with a recent lower limb or pelvic fracture. Unlike previous post-fracture studies, the intervention and follow-up will be long-term, and the majority of exercise will be undertaken independently, aiming for a balance between sufficient intensity for effectiveness and reduced cost for feasibility of implementation.

### Primary objective:

To compare the effect of an exercise and fall prevention self-management program with usual care on mobility-related disability and falls in older people with a recent fall-related lower limb or pelvic fracture.

### Secondary objectives

To compare the effect of an exercise and fall prevention self-management program versus usual care on balance and mobility, falls risk, physical activity, walking aid use, frailty, pain, nutrition, falls efficacy, mood, positive and negative affect, quality of life, assistance from others, hospital readmission, and health-system and community-service contact in older people with a recent fall-related lower limb or pelvic fracture.To establish the cost-effectiveness and cost-utility of the intervention approach, compared with that of usual care, from the perspective of the health and community care funder.To describe the safety and tolerability of the program.To determine features associated with uptake of the intervention.

## Methods / design

### Design

A randomised controlled trial will be conducted among 350 people aged at least 60 years with a recent fall-related lower limb or pelvic fracture that led to a hospital admission. Fig. 1 gives an overview of the study design. The Northern Sydney Central Coast Human Research Ethics Committee approved this study (Research Protocol Number 0905-089 M) as did local committees at the recruitment sites. All participants will give written informed consent prior to randomisation. The study adheres to the CONSORT guidelines [25] and is registered with the Australia New Zealand Clinical Trials Register ACTRN12610000805077.

**Fig. 1 Fig1:**
[figure not shown]
Overview of the flow of participants through the RESTORE trial

### Participants

Participants will be recruited from Royal North Shore, Prince of Wales, Manly, St George, Mona Vale, Gosford, War Memorial, John Hunter, Royal Newcastle, Longueville Private, Greenwich and Orange Hospitals - all in New South Wales, Australia. Potential participants will be identified in hospital via discussion with hospital staff and review of ward lists. In addition, letters will be sent to potentially eligible people identified from hospital databases, and general advertisement in hospitals, community centres and newspapers will be undertaken.

Participants who meet the following inclusion criteria will be invited to participate: female or male; aged 60 years or older; fall-related lower limb or pelvic fracture in the past two years; no marked cognitive impairment (Mini-Mental State Examination score [26] ≥ 24); living at home or in a hostel (low care residential acre facility where residents generally live in their own units but meals are provided and assistance with showering and dressing in available), in the Sydney, Central Coast, Hunter or Orange regions of New South Wales, Australia.

People will be ineligible to participate in the trial if they meet the exclusion criteria: insufficient English language skills to complete the study assessment and interventions; unable to walk 10 metres despite assistance from a walking aid or another person; progressive neurological disease (e.g., Parkinson’s disease); a medical condition precluding exercise e.g., unstable cardiac disease, uncontrolled hypertension, uncontrolled metabolic diseases, large abdominal aortic aneurysm; currently receiving a treatment program from a rehabilitation facility.

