### Statistical analysis

The effect of group allocation on continuous outcomes will be assessed using linear regression models in which pre-test performance is a covariate. The number of falls per person-year will be analysed using negative binomial regression to estimate the between-group difference in fall rate [43]. The difference between the proportions of fallers in each group will be calculated using the relative risk statistic. Longitudinal analyses will be used to assess the effects on the variables measured each 3 months. Logistic regression models will be used to compare groups for dichotomous outcomes. Additional regression analyses will establish predictors for program adoption and adherence and cost-effectiveness. Sub-group analyses will be conducted using only participants with hip fracture to enable these data to be used in systematic reviews. Data will be coded to permit blinding to group allocation in the statistical analysis and the primary analyses will be conducted in accordance with the intention-to-treat principle [44]. Analyses will be conducted using the Stata software package, College Station, Texas.

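### Eligibility reaches back two years after fracture, but the mobility models name only the baseline score as a covariate; prespecifying time since fracture would add a small, nearly free gain in precision

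*Protocol article*

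**What the plan says.** All references are to the protocol article.

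- **Population in the objective and design.** The primary objective is the effect "on mobility-related disability and falls in older people with a recent fall-related lower limb or pelvic fracture". The Design section describes people "with a recent fall-related lower limb or pelvic fracture that led to a hospital admission". Neither gives a time limit.
- **Eligibility.** The Participants section sets the only limit: "fall-related lower limb or pelvic fracture in the past two years". Recruitment uses ward lists and hospital staff, and also letters to people found in hospital databases and general advertising.
- **Early phase.** The abstract says that those who "have completed active rehabilitation, will be recruited". The exclusions include people "currently receiving a treatment program from a rehabilitation facility". No minimum time since fracture is given.
- **Allocation.** Randomisation and blinding describes concealed central randomisation in permuted blocks and names no stratification factor.
- **Analysis.** Continuous outcomes are analysed by "linear regression models in which pre-test performance is a covariate". Three-monthly measures get longitudinal analyses, with no covariates named. One subgroup is planned: "Sub-group analyses will be conducted using only participants with hip fracture".
- **Power.** The Sample size calculation states 90% power for a 10% difference in CSPS with 175 per group.

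**The concern.** Time since fracture probably predicts how much a participant will change over 12 months without any intervention. The baseline score carries part of that information but not all of it. A given CSPS may be a point on a rising curve in an early case and a settled deficit in a late one, so expected change differs at equal baseline.

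The recruitment routes make a wide spread likely: wards supply fresh fractures, while databases and advertisements can supply old ones. If the mobility models condition on the baseline score alone, the predictable part of natural recovery stays in the residual error. Any chance difference between arms in time since fracture then passes into the estimate uncorrected.

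At stake is precision for the mobility outcomes: CSPS, LLFDI disability component and AM-PAC. The falls model is not part of this point.

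**Working it through.** **1. The plan's own figure.** The stated 90% power cannot be reproduced, because no mean, SD or baseline correlation is given. It can be back-solved with the two-sample normal formula, assuming two-sided alpha of 0.05:

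delta/SD = (1.960 + 1.282) × √(2/n)

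- n = 175 per group: 3.2415 × √(2/175) = 0.347
- n = 175 × 0.85 = 148.75, after 15% dropout: 0.376
- with 15% dilution for non-compliance as well: 0.376/0.85 = 0.442

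The 90% is therefore taken as the starting point and neither confirmed nor refuted.

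**2. How far expected natural change varies (assumed).** Suppose the deficit decays as B·exp(−T/τ), where T is months since fracture at baseline. The natural 12-month gain is then

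gain = B·exp(−T/τ)·(1 − exp(−12/τ))

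With B = 1 SD and τ = 3 to 6 months (assumptions, not figures from the document):

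| T at baseline | τ = 3 | τ = 6 |
|---|---|---|
| 2 months | 0.50 SD | 0.62 SD |
| 18 months | 0.00 SD | 0.04 SD |

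The direction is plausible. The size depends on B, τ and how many participants enter early.

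**3. Residual variance removed.** Simulation with plateau SD 1, B = 1, measurement SD 0.4 and times uniform up to 24 months. The model for the 12-month score given baseline was fitted with and without log T and its square.

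| Earliest entry | Cut in residual variance, τ = 3 to 6 |
|---|---|
| 1 month | about 5.4 to 7.2% |
| 3 months | about 1.5 to 4% |
| 6 months | about 0.2 to 1.6% |

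Two sensitivities apply to entry from 3 months:

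- Letting deficit and time constant vary between people (log-SD 0.5) and adding unrelated 12-month change (SD 0.5) reduces the cut to about 1 to 2%.
- Concentrating entry strongly in the early months (times placed at 3 + 21u², u uniform) raises it to 3.9 to 6.7% without that individual variation and 2.2 to 3.1% with it.

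The one-month row is too favourable, because participants must have finished active rehabilitation. About 0.2 to 5% is a fair working range.

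**4. Effect on power.** If the 90% already reflects the mixed population, adjustment that removes a share R² of residual variance gives

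power = Φ(3.2415/√(1 − R²) − 1.960)

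| R² | Power after adjustment | Unadjusted N for the same precision, 350/(1 − R²) |
|---|---|---|
| 0.002 | 90.1% | 351 |
| 0.01 | 90.3% | 354 |
| 0.02 | 90.6% | 358 |
| 0.05 | 91.4% | 369 |

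If instead the planning SD left this variation out, unadjusted power is Φ(3.2415·√(1 − R²) − 1.960): 89.7% at R² = 0.01 and 88.5% at R² = 0.05.

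**The case against.** **The statistical section is condensed, and further covariates may be in an analysis plan that is not shown.** This stands in part: the absence of a covariate from an article is not an error. But the article does state the model and names one covariate for it, and the suggestion improves on that stated model. If the analysis plan already includes time since fracture, the point is met.

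**The gain is small and rests on assumed curves.** This stands. The document gives no recovery curve and no distribution of time since fracture, and completed rehabilitation removes part of the steep phase. Pre-test performance also absorbs some of the recovery stage.

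**A reader might infer that natural recovery biases the comparison.** It does not. Allocation is randomised and concealed, so time since fracture is balanced in expectation, and the standard error already allows for chance imbalance. Adjustment removes a chance difference when one occurs; it does not repair a systematic one.

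**A reader might infer that the result cannot be tied to recent fracture, or that the objective promises faster recovery.** The documents support neither. The two-year criterion is the trial's own working limit for 'recent', and the Discussion presents broad inclusion criteria as a strength. The primary objective only compares the programme with usual care. The undefined word is a matter of clarity.

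**An interaction test would have low power.** This stands, so it is not part of the required change.

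**Conclusion.** The point holds as a modest improvement in precision. The stated mobility models omit a baseline variable that probably predicts 12-month change beyond the baseline score, in a trial whose entry window makes that variable vary widely. Validity is not affected.

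The likely gain is about 0.2 to 5% of residual variance, or 0.1 to 1.4 percentage points on the stated 90% power. This rests on exponential recovery with a time constant of 3 to 6 months, an initial deficit of 1 SD, and few participants entering in the first months. A sample dominated by early cases would gain somewhat more. Marked variation between people in the course of recovery would reduce the gain.

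**What to change.** Before unblinding, prespecify time since fracture at baseline (for example log months, with a squared term if wanted) as a covariate in the linear models for CSPS and the LLFDI disability component and in the longitudinal AM-PAC model. Some measure of fracture timing is already needed to apply the two-year criterion, and Data collection provides for fracture details. The cost is one or two degrees of freedom and a line of analysis-plan text. Eligibility, treatment and sample size do not change.

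As a minor clarification, state the two-year limit where the primary objective and Design section say 'recent', and report the distribution of time since fracture by arm. A treatment-by-time-since-fracture interaction on a mobility outcome is optional. If included, label it exploratory and report it with its confidence interval.

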### Intervention

Prior to commencement of the intervention, medical clearance for study participation will be obtained from each participant's medical practitioner.


The study physiotherapists will be experienced in prescribing exercise for older people. Strategies to optimise adherence to the intervention include goal setting and review at each home visit, scheduling exercise, provision of a home exercise manual that can be updated at each visit by the physiotherapist, and an exercise diary. Further strategies to increase adherence are outlined in Additional file 1. If a participant becomes unwell or is admitted to hospital, the program will be resumed when the participant feels able and the relevant treating professionals deem the participant well enough to participate again.

#### Fall prevention education

Intervention group participants will also be offered the “Stepping On” program [24] (http://www.steppingon.com) as implemented by the New South Wales Ministry of Health (i.e., weekly 2-hour group sessions for seven weeks). The “Stepping On” program is a multi-faceted community based program co-ordinated by an occupational therapist or other health professional in a small-group learning environment. It uses a variety of strategies to increase self-efficacy in fall-risk situations, [27] incorporates a decision-making model to explore barriers and options for reducing risk of falls [28], and uses adult learning principles to self-manage risk [29]. The “Stepping On” content is relevant to people with fall-related lower limb or pelvic fracture and will cover coping with visual loss and regular visual screening, medication management, environmental and behavioural home safety, and community safety [30]. Group sessions will be held in rooms at local community centres or hospitals. Transport will be arranged for those who would otherwise be unable to attend the sessions. Each program will be attended by up to 13 people. The group session will be completed within the 12-month study period, with the timing depending on availability of a “Stepping On” program. The “Stepping On” program encourages the older person to take control and explore different coping behaviours, and encourages follow-through of safety strategies in everyday life. The program addresses each of the eight aspects of the Health Education Impact Questionnaire [31]: positive and active engagement in life, health-directed behaviour, skill and technique acquisition, constructive attitudes and approaches, self-monitoring and insight, health service navigation, social integration and support, and emotional wellbeing.

If participants are unable or unwilling to attend the group-based “Stepping On” program, the physiotherapist will provide them with individualised advice, the weekly “Stepping On” handouts and/or, if deemed appropriate, a publication targeting falls prevention during the scheduled home visits [32]. Verbal advice on fall prevention will be provided to intervention group participants during most home visits.

#### Control group

Participants assigned to the control group will receive the usual care available to older people from their medical practitioners and community services. In the catchment areas for the trial, usual care for non-institutionalised older people may involve allied health input, medical management of health conditions, assessment of care needs, and provision of care. Full documentation of usual care is beyond the scope of this trial.

